## Abstract

**Background:**

The growing use of cannabis in adolescence is a public health problem that must be addressed through prevention. In Spain, the average age of initiation of cannabis use in the adolescent population is 14.8 years. At 14 years, the lifetime prevalence of cannabis use is 11.7%, which increases to 51.,5% at the age of 18; the prevalence of cannabis use in the population aged 14 to 18 years is 28.6%, a figure that must be tried to reduce, that is why this school prevention program is proposed: Alerta Cannabis.

**Methods:**

The Alerta Cannabis research project consists of design, implementation, and evaluation. In the first phase, a computer-tailored eHealth program (Alerta Cannabis) is developed based on the I-Change Model, an integrated model based on three main behavioral change processes: awareness, motivation, and action. This program consists of four 30-minute sessions that will provide culturally adapted and personalized advice to motivate students not to use cannabis through text feedback, animations, and gamification techniques. This phase will also include usability testing. In the implementation phase, secondary school students from Western Andalusia, Spain (Seville, Cádiz, Huelva, and Córdoba) and Eastern Andalusia (Jaén, Málaga, and Granada) will be randomized to an experimental condition (EC) or a control condition (CC) for a cluster randomized clinical trial (CRCT). Each condition will have 35 classes within 8 schools. GI will receive the online intervention Alerta Cannabis. EC and CC will have to fill out a questionnaire at baseline, six months, and twelve months of follow-up. In the last phase, the effect of Alerta Cannabis is evaluated. The primary outcomes are the lifetime prevalence of cannabis use and its use in the last 30 days and at 6 months. At 12 months of follow-up, the prevalence in the last 12 months will also be assessed. The secondary outcome is the intention to use cannabis.

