## Introduction

Cannabis is the most widely consumed illegal drug in the world and with the general populations and adolescent populations in Europe, Spain, and Andalusia. According to the World Drug Report of the United Nations Office on Drugs and Crime [1], 209 million people used cannabis in the previous year. Furthermore, cannabis consumption is increasing; globally, the number of cannabis users has increased by 23% in the last decade. Cannabis use is more common among 15 to 16-year-olds (5.8%) than in the general population (4.1%). In Spain [2–4], the average age of initiation of cannabis use in the adolescent population is 14.8 years. At 14 years of age, the lifetime prevalence of cannabis use is 11.7%, which quintuples to 51.5% at 18 years old; the prevalence of cannabis use in the population aged 14 to 18 years is 28.6%. Among those under 18 years of age, cannabis is consolidated as the substance that generates the highest treatment admissions (95.1%).In Andalusia [3, 5], the lifetime prevalence of cannabis use in the population aged 14 to 18 is 21.4%, and cannabis use is the leading cause of treatment admissions for substance use in the adolescent population (86%). Recent scientific literature concludes that there is insufficient evidence regarding the association between cannabis use and all-cause mortality [6, 7]. However, some adverse health outcomes may be elevated among heavy cannabis users, such us fatal motor vehicle accidents, and possibly respiratory and brain cancers [6]. Furthermore, cannabis use disorder is a common comorbidity and risk marker for self-harm, mortality, and death by unintentional overdose and homicide among youth with mood disorders [8]. In fact, cannabis use is the drug associated with the highest number of disorders related to mental health [9].

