
Research indicates that cannabis prevention programs can be effective if they use social cognitive models to convince adolescents of their disadvantages, how to deal with social influences that promote their use, and to increase self-efficacy and refusal skill [10, 17–19]. They also concluded that programs that incorporated elements of several prevention models were significantly more effective than those based solely on a social influence model [18, 19]. In addition, eHealth methods are also effective for cannabis treatment and have even better results for prevention [17]. In this line and view of the results of other investigations, the cultural compatibility of the prevention interventions must also be considered [20–23].

Based on this scientific evidence the school-based program Alerta Cannabis will be developed. It will use as theoretical model the Integrated Change Model [24], which has also turned out to be an explanatory model for the factors associated with the use of cannabis among Andalusian adolescents [25]. This model integrates existing social cognitive models and can be used as a basis in computer-tailored information and communication technology.

The starting hypothesis is that the application of this program, Alerta Cannabis, to minors between the ages of 14 and 18 in the school context, will be effective in reducing the prevalence of cannabis use. The objective of this study is to evaluate the effect of the Alerta Cannabis program, for which we will consider, as primary outcomes, different patterns of cannabis use such as cannabis use sometimes in life, in the last 30 days and the last 12 months, and, as a secondary outcome, the intention to use cannabis.

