#### Participants

The target population will be students between the ages of 14 and 18 enrolled in the third and fourth years of Compulsory Secondary Education (CSE), the first year of high school or intermediate training cycles of publicly affiliated Secondary Education Institutes (SEI) in Andalusia, equivalent to grades 9, 10, 11 and 12, respectively, in the United States. The inclusion criteria in the study for schools are: 1) Secondary School in Andalusia; 2) having access to the Internet; and 3) allowing the use of computers, mobile phones, or tablets to carry out the activity. The exclusion criteria for the students are: 1) having previously participated in a specific program for the prevention of cannabis use 2), having difficulties in the language of the program (Spanish) 3), not wanting to participate or not having parental consent to participate.

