## Evaluation phase

### Effectiveness and process evaluation

General descriptive statistics will be used to describe the baseline characteristics of the participants. Since the students will be nested within a class in the study and classes will be nested within schools, to examine the predictors of dropout versus non-dropout, a multilevel logistic regression analysis will be conducted. In addition, a multilevel approach will be used to assess the effects of the intervention on the behavior of cannabis use. The first level will be repeated measures within the participants (baseline and two follow-up measurements), the second level will be the student, the third level is the class, and the fourth level is the school.

Baseline cannabis will use behavior and the demographic variables described above will be included as covariates. To select significant predictors and interactions, a backward deletion procedure (a = 0.05) will be used, with the restriction that predictors will not be removed from the model if they were involved as terms.

To study the predictors of adherence, we will also analyze the associations between the potential characteristics (i.e., gender, age, academic course, religion, nationality, family wealth score, Apgar score, and cannabis use at baseline) on the one hand, and participation in the intervention (i.e., adherent or not) through the number of sessions attended by participants at schools on the other.

Finally, for the process evaluation, a descriptive analysis will be performed using chi-square tests to examine differences between males and females and between cannabis users and non-users. We use SPSS Statistics for Windows, version 26.0 (IBM Corp.), for these analyses.

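### Lifetime use is a primary outcome in students who may already have used cannabis; about 21–29% of them cannot change on it, which dilutes the comparison

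*Protocol article*

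**What the plan says.** The abstract's Methods paragraph reads: "The primary outcomes are the lifetime prevalence of cannabis use", and it names recent use alongside. The Introduction repeats the choice in the objective, listing "different patterns of cannabis use such as cannabis use sometimes in life, in the last 30 days and the last 12 months" as primary outcomes. It frames the hypothesis as a programme that "will be effective in reducing the prevalence of cannabis use".

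Under Participants, "The target population will be students between the ages of 14 and 18". The student exclusions are earlier exposure ("having previously participated in a specific program for the prevention of cannabis use"), language difficulty, and refusal or lack of parental consent. None concerns earlier cannabis use, and no section limits the lifetime outcome to students who had never used.

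On baseline use, the Introduction says of Andalusia that "the lifetime prevalence of cannabis use in the population aged 14 to 18 is 21.4" per cent. For Spain it gives 28.6% at ages 14 to 18 without repeating the word lifetime, and lifetime figures of 11.7% at age 14 and 51.5% at age 18.

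Under Effectiveness and process evaluation, the effect model is multilevel. Its first level is the repeated measurements, with baseline counted among them. The same section adds: "Baseline cannabis will use behavior and the demographic variables described above will be included as covariates". It does not say which baseline measure is meant, and it uses the word logistic only for the dropout model.

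**The concern.** Lifetime use is an absorbing state. A student who has used by baseline has the same outcome at both follow-ups whatever the programme does. Such students carry no information about the effect, but they add the same block of positives to both arms. That shrinks the difference in prevalence and moves both proportions towards the middle of the scale, where the variance is larger. A programme that really delays first use could look ineffective on a primary outcome meant to capture prevention.

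There is a related modelling question. If the baseline covariate is lifetime use, every baseline ever-user has outcome 1 at follow-up. What this does to the estimated effect depends on whether the baseline measurement is also kept as an outcome.

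**Working it through.** The article gives no effect size or power for lifetime use. The Sample size section concerns 30-day use, so there is no stated figure to reproduce for this outcome.

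**Inputs.** From the article: n = 875 per arm; baseline lifetime use p0 = 21.4% or 28.6%. Assumed, because the article gives no onset rate: 12-month onset among never-users of c = 10% in control and t = 7% with the programme. The range is widened below.

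**Students who cannot change.** p0 × n:
- 0.214 × 875 = 187 per arm
- 0.286 × 875 = 250 per arm

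By age the share would run from 11.7% at 14 to 51.5% at 18.

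**Dilution.** Follow-up lifetime prevalence is p0 + (1 − p0) × onset, so the arm difference is (1 − p0)(c − t).

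| p0 | Control | Programme | Difference, all students | Difference, never-users |
|---|---|---|---|---|
| 21.4% | 0.214 + 0.786 × 0.10 = 29.3% | 0.214 + 0.786 × 0.07 = 26.9% | 2.36 points | 3 points |
| 28.6% | 0.286 + 0.714 × 0.10 = 35.7% | 0.286 + 0.714 × 0.07 = 33.6% | 2.14 points | 3 points |

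**Information.** Per student enrolled in each arm, information is the squared difference divided by the summed binomial variances. For the subset it is multiplied by (1 − p0), because only never-users contribute.
- p0 = 21.4%: all students 0.02358² / (0.2926 × 0.7074 + 0.2690 × 0.7310) = 0.00138; never-users 0.786 × 0.03² / (0.10 × 0.90 + 0.07 × 0.93) = 0.00456. Ratio 3.3.
- p0 = 28.6%: all students 0.02142² / (0.3574 × 0.6426 + 0.3360 × 0.6640) = 0.00101; never-users 0.714 × 0.03² / 0.1551 = 0.00414. Ratio 4.1.

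The ratio is how many times more students an unadjusted whole-sample comparison must enrol for the same expected test statistic, ignoring clustering.

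**Range.** Keeping the 30% relative reduction, the same formula gives ratios of 5.8 and 7.5 at 5% onset and 2.0 and 2.4 at 20% onset, for p0 of 21.4% and 28.6% respectively. With 10% against 5% onset and p0 = 21.4%, power at 875 per arm is 45% in all students and 94% in never-users ignoring clustering. Using the article's intracluster correlation of 0.2 and 25 per class, it is 12% and 37%.

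**Model behaviour.** These are single-level logistic fits to simulated data for 1,750 students, without class or school effects.
- *Follow-up rows only, baseline lifetime use as covariate.* The baseline coefficient diverges (20 to 41 as iterations rise), but the arm effect is finite. With one follow-up it equals the never-user estimate: log odds ratio −0.928, SE 0.202 in both. The reason is algebraic: as the baseline coefficient grows, the ever-users' likelihood tends to 1 and only the never-users' likelihood remains.
- *Baseline as outcome row and as covariate, with arm, time and arm × time.* The intercept, time and baseline coefficients diverge, and the SEs of the arm × time terms exceed 1,000,000, so Wald tests of the effect are unusable. Without the arm main effect, those SEs are 0.30 and 0.22, so the failure depends on the double use of baseline together with that term.
- *Baseline 30-day use as covariate instead* (25% ever-users, half of them assumed to be 30-day users). The baseline coefficient again diverges. The remaining ever-users still dilute the effect: log odds ratio −0.24 against −0.60 in never-users.
- *2% to 5% of ever-users recant at follow-up.* With lifetime use as covariate, the baseline coefficient becomes finite, about 5 to 6.

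**The case against.** The strongest reply is that dilution and model trouble do not both apply at full strength. The 3.3 to 4.1 figure is for an unadjusted comparison, whereas the article plans adjustment for baseline use. If that covariate is lifetime use and only follow-up rows are outcomes, adjustment removes the dilution and returns the never-user effect. This stands as far as it goes. But the article does not name the measure, 30-day use would remove the dilution only in part, and the section as written keeps baseline as an outcome row as well.

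Two stronger readings are tempting, and the article supports neither. A reader might infer that adjusting for baseline lifetime use breaks a logistic model. The effect model is not called logistic, the covariate is not named, the diverging coefficient is a nuisance term, and recanted answers would make it finite. Non-convergence of the four-level model has not been shown. A reader might also infer that the hypothesis cannot be met because lifetime prevalence in a followed cohort only rises. The hypothesis speaks of prevalence of use in general, and a lower lifetime prevalence than control is attainable, as 26.9% against 29.3% shows.

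It is also fair to say that the trial is sized on 30-day use, which can reverse and is unaffected, and that a condensed article may leave the covariate, link and analysis set to a fuller document. The choice of lifetime prevalence as a primary outcome in an unrestricted cohort, and the two roles given to baseline, are nevertheless stated in the article itself.

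**Conclusion.** The point holds as a loss of sensitivity, not as invalidity. The share of students who cannot change, about 21% to 29%, rests on the article's survey figures applying to the enrolled classes, with 28.6% read as lifetime use. The loss of 0.6 to 0.9 points out of 3, and the sample multiple of 3.3 to 4.1, rest on the assumed 10% and 7% onset. Over 5% to 20% onset at the same relative reduction, the multiple runs from about 2 to 7.5, so the direction is firm and the size is not.

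The modelling part is conditional. If the covariate is baseline lifetime use, its own coefficient cannot be estimated, barring recanted answers. The intervention effect remains estimable from follow-up rows. Its inference is at risk only where baseline serves as both outcome row and covariate, which is what the analysis section literally describes.

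**What to change.** - Define the lifetime outcome as first use by 6 and by 12 months among students reporting no lifetime use at baseline, and analyse it in that subset.
- Keep 30-day and 12-month use as outcomes for all students.
- Name the baseline measure, and use baseline either as a covariate or as an outcome row, not both.
- State the expected direction for this outcome as lower onset than in the control condition.

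The cost is wording and a filter, since lifetime use is already in the baseline questionnaire. The price in interpretation is that the onset result applies to baseline never-users only. With strong clustering, its power may still be modest, as the 37% in the example shows.

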**Discussion:**

The study tests the effect of the innovative program specifically aimed to reduce the use of cannabis in the adolescent population through eHealth in Spain. The findings aim to develop and implement evidence-based cannabis prevention interventions, which could support school prevention, for instance, the assistance of school nurses. If the program proves to be effective, it could be useful to prevent cannabis use on a national and international scale.

**Trial registration:**

NCT05849636. Date of registration: March 16, 2023.

## Introduction

Cannabis is the most widely consumed illegal drug in the world and with the general populations and adolescent populations in Europe, Spain, and Andalusia. According to the World Drug Report of the United Nations Office on Drugs and Crime [1], 209 million people used cannabis in the previous year. Furthermore, cannabis consumption is increasing; globally, the number of cannabis users has increased by 23% in the last decade. Cannabis use is more common among 15 to 16-year-olds (5.8%) than in the general population (4.1%). In Spain [2–4], the average age of initiation of cannabis use in the adolescent population is 14.8 years. At 14 years of age, the lifetime prevalence of cannabis use is 11.7%, which quintuples to 51.5% at 18 years old; the prevalence of cannabis use in the population aged 14 to 18 years is 28.6%. Among those under 18 years of age, cannabis is consolidated as the substance that generates the highest treatment admissions (95.1%).In Andalusia [3, 5], the lifetime prevalence of cannabis use in the population aged 14 to 18 is 21.4%, and cannabis use is the leading cause of treatment admissions for substance use in the adolescent population (86%). Recent scientific literature concludes that there is insufficient evidence regarding the association between cannabis use and all-cause mortality [6, 7]. However, some adverse health outcomes may be elevated among heavy cannabis users, such us fatal motor vehicle accidents, and possibly respiratory and brain cancers [6]. Furthermore, cannabis use disorder is a common comorbidity and risk marker for self-harm, mortality, and death by unintentional overdose and homicide among youth with mood disorders [8]. In fact, cannabis use is the drug associated with the highest number of disorders related to mental health [9].

A meta-analytic review [10] by Porath-Waller and Cols (2010) concluded that school-based programs have a positive impact on reducing adolescents‘ (aged 12–19) cannabis use compared to control conditions. Their results also suggested that targeting high school students is more effective than targeting middle school students. In Spain, the Ministry of Health has a system of health promotion and prevention that includes school-based health education in schools [11]. This is linked to the Strategy for Health Promotion and Prevention of the National System of Health. This includes a website for healthy lifestyles, a map of resources for health and the Information System of Health Promotion and Education (SIPES), where it is possible to publish actions that are carried out by different organizations at regional and national levels. Furthermore, a portal to include Good Practices for the reduction of demands for substance use and other addictions [12], with the objective of promoting the quality of interventions in Spain, that is to identify, select, transfer, and disseminate good practices in addictions. However, a review of school programs for substance abuse prevention in Spain indicated promising results although a lack of more rigorous evaluation is detected [13]. Moreover, a recent review concludes that most of the programs include in Spanish best practices portals did not evaluate their efficacy, while there are programs that having had their results evaluated are not indexed in said portals. Although Spain goes in the right direction, an evidence-based prevention model coexists with a pseudo-preventive model. Therefore, it is necessary to continue to promote a culture of evidence-based prevention and having efficacy evaluation protocols in prevention programs [14]. This review recommends the programs due to their strong evidence the Project EX and the Unplugged program. The last is a comprehensive program for substance use prevention based on the social influence approach and showed a reduction in the prevalence of cannabis. However, the data were not disaggregated by countries (the study was carried out in Seven European countries: Austria, Belgium, Germany, Greece, Italy, Spain, and Sweden) [15]. Moreover, in northern Spain, a universal program on drug use in general [16], ‘Be yourself’, showed a positive impact on the reduction of cannabis use in middle schools (aged 12–14) exposed to the intervention. The latter is based on models of social influence and social competence.

Research indicates that cannabis prevention programs can be effective if they use social cognitive models to convince adolescents of their disadvantages, how to deal with social influences that promote their use, and to increase self-efficacy and refusal skill [10, 17–19]. They also concluded that programs that incorporated elements of several prevention models were significantly more effective than those based solely on a social influence model [18, 19]. In addition, eHealth methods are also effective for cannabis treatment and have even better results for prevention [17]. In this line and view of the results of other investigations, the cultural compatibility of the prevention interventions must also be considered [20–23].

Based on this scientific evidence the school-based program Alerta Cannabis will be developed. It will use as theoretical model the Integrated Change Model [24], which has also turned out to be an explanatory model for the factors associated with the use of cannabis among Andalusian adolescents [25]. This model integrates existing social cognitive models and can be used as a basis in computer-tailored information and communication technology.

The starting hypothesis is that the application of this program, Alerta Cannabis, to minors between the ages of 14 and 18 in the school context, will be effective in reducing the prevalence of cannabis use. The objective of this study is to evaluate the effect of the Alerta Cannabis program, for which we will consider, as primary outcomes, different patterns of cannabis use such as cannabis use sometimes in life, in the last 30 days and the last 12 months, and, as a secondary outcome, the intention to use cannabis.

### The integrated change model

The I-Change model is a behavior change model that tries to generate motivational and behavioral change in individuals based on their intentions and abilities [24]. The I-Change model integrates various theoretical models such as the Attitude Model- Social Influence-Self efficacy (or ASE-model) [26], the Theory of Planned Behavior by Ajzen [27, 28], Bandura’s Social Cognitive Theory [29], Transtheoretical Model of Change [30], Belief Model on Health and Goal Setting [31]. Behavior change is generated through three stages: pre-motivational, motivational, and post-motivational, with the motivational stage serving as the foundation [25]. Pre-motivational factors influence behaviors and consist of predisposing factors (behavioral, psychological, biological, social, and cultural), awareness factors (knowledge, cues to action, and risk perception), and information factors (message, channels, and source), which. Motivational factors, facilitate or condition action. They include attitude (advantages and disadvantages), social influence (social norm, social pressure, social model, support), and self-efficacy (barriers, emotions, and abilities), while post-motivational factors are related to skills (implementation plans, development skills, and actions objectives) (Fig. 1), which are key to convert intentions into actions [32, 33].

